#### Sample size calculation for the secondary outcome

Sample size is estimated for the secondary outcome (failure of patency at 6 months) under assumptions of additive or multiplicative effects for each of 3 placebo rates. The calculation below is based on the following assumptions: 5% loss to follow up, 15% drop-in and 5% drop-out. The baseline failure rate of patency at 6 months is (40%, 50% and 60%) in the placebo group, the use of either aspirin or omega-3 fatty acids alone results in a relative risk reduction (RRR) of 25%, i.e. the failure rate becomes respectively 30%, 37.5% and 45% for a patient taking only one drug.

The sample size calculation is based on a marginal analysis (Z-test) with two-sided α = 0.05, power β = 90%. Table 2 presents required sample sizes under additive model (bold) and under multiplicative model

**Table 2 T2:** The sample sizes required under the additive and multiplicative models for the secondary outcome – functional patency

	Total sample size			
	
	Additive model		Multiplicative model	
	
Patency failure rate at 6 months for placebo group	unadjusted	adjusted	unadjusted	adjusted
40%	**874**	**1455**	1156	1812
50%	**620**	**1034**	820	1297
60%	**452**	**752**	596	941

(Unadjusted and adjusted refer to the calculations of sample size without and with adjustment for loss to follow-up (5%), drop-in (15%) and drop-out (5%))

A recently published comparable trial in the United States [16] experienced a placebo rate of 60% for failure of patency at 6 months. We are confident that a sample size based on a placebo rate of at least 50% is a realistic estimate and that the sample of 1,200 recruited for the primary outcome will generally be adequate for the secondary outcome whether the effect is additive or multiplicative.

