## Abstract

**Background:**

Haemodialysis (HD) is critically dependent on the availability of adequate access to the systemic circulation, ideally via a native arteriovenous fistula (AVF). The Primary failure rate of an AVF ranges between 20–54%, due to thrombosis or failure of maturation. There remains limited evidence for the use of anti-platelet agents and uncertainty as to choice of agent(s) for the prevention of AVF thrombosis. We present the study protocol for a randomised, double-blind, placebo-controlled, clinical trial examining whether the use of the anti-platelet agents, aspirin and omega-3 fatty acids, either alone or in combination, will effectively reduce the risk of early thrombosis in de novo AVF.

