1. The high functional failure rate is especially concerning and much higher than expected. This may reflect aspects related to surgical (e.g. small number of procedures performed by individual surgeons) and nursing care (needling skills for AVF) in the US and/or patients demographics. Furthermore, significant variation between USA and both European and Australian clinical practice could explain the high US study failure and unsuitability rates. In this context, the generalisability of this American study to other countries is uncertain and justifies additional trial confirmation in other countries;

2. Earlier administration of the active agents before surgery (as in FAVOURED) rather than after may lead to an even greater efficacy in relation to the primary thrombosis rate;

3. The rational for trialing two agents in a factorial design remains valid. Omega-3 fatty acids may be of an additional benefit to aspirin by improving vascular endothelial function and smooth muscle relaxation, which may enhance maturation and greater attainment of functional patency;

4. The low bleeding rates and safety data with Clopidogrel are reassuring in the context of uncertainty regarding the safety of anti-platelet therapy in renal failure, given that anecdotally Clopidogrel is considered to be associated with a higher risk of bleeding than aspirin;

5. The greater duration of follow up (minimum of 1 year) in the FAVOURED Study will allow greater ascertainment of the secondary outcome measure with relation to functional patency. This acquires even greater importance in view of the Clopidogrel Study result.

If the trial demonstrates a positive effect of either or both agents, this will support routine use of these agents in clinical practice and lead to a widespread reduction in thrombosis and an increase in functioning AVF. This has significant patient benefits and health system benefits in reduced costs associated with repeat hospitalisations. If the trial demonstrates no effect of the agents, this will suggest that platelet aggregation is not the major mechanism for thrombosis in this population and that efforts to improve AVF patency would then need to be redirected to other mechanisms associated with access failure, such as vascular anatomical function.

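### The 6-month placebo failure rate of at least 50% rests on a US rate that the Discussion doubts, so the assurance that 1,200 patients suffice for functional patency at 90% power under either model is unsupported

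*Protocol article*

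**What the plan says.** The section on sample size for the secondary outcome plans for 90% power with a two-sided 5% marginal Z-test. It assumes a 25% relative risk reduction for either drug alone and allows for "5% loss to follow up, 15% drop-in and 5% drop-out". Three placebo rates are tabulated: "The baseline failure rate of patency at 6 months is (40%, 50% and 60%) in the placebo group". Table 2 gives these adjusted totals (additive/multiplicative):

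- 40%: 1,455/1,812
- 50%: 1,034/1,297
- 60%: 752/941

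Below the table, the text cites a US trial, described as comparable, with 60% failure on placebo. It then states: "We are confident that a sample size based on a placebo rate of at least 50% is a realistic estimate". From this it concludes that 1,200 will generally be adequate whichever model holds.

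The Discussion reports the same trial, with failure of suitability for dialysis in 60% of its placebo group. Its first listed implication begins "The high functional failure rate is especially concerning and much higher than expected". It suggests that surgical volume, needling skills or patient mix may be responsible, says that differences between US and Australian or European practice could explain the rate, and concludes that "the generalisability of this American study to other countries is uncertain". The Discussion paragraph of the Abstract likewise stresses differences from that trial in surgical and patient demographics.

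**The concern.** The US figure is put to two uses that pull against each other. When the sample is sized, it comes from a comparable trial and supports a floor of 50%. When a further trial is justified, it is unexpectedly high and may not transfer to Australia and New Zealand. If the second view is taken seriously, the local rate could well be lower than 60%, and nothing in the document shows that the fall stops at 50%. No local estimate of 6-month functional failure is cited.

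The power statement for functional patency is at stake. The Discussion says this outcome has gained importance since the US result. A null finding would be read against a claim of adequate size that depends on the doubtful rate.

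**Working it through.** **Inputs** (all from the secondary sample size section): two-sided alpha 0.05; power 90%; relative risk reduction 25% per drug; drop-in 15%, drop-out 5%, loss 5%; placebo rates p of 40%, 50% and 60%. Equal allocation to four groups (Study Procedures) gives 1:1 margins. The total is 1,200.

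**Step 1: marginal rates.** The cells are p, 0.75p, 0.75p and, for both drugs, 0.5p (additive) or 0.75 × 0.75 × p = 0.5625p (multiplicative).

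- Control margin: c = (p + 0.75p)/2
- Active margin: t = (0.75p + 0.5p)/2 or (0.75p + 0.5625p)/2

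**Step 2: reproduce Table 2, unadjusted.** n per margin = (1.960 + 1.282)² × [c(1−c) + t(1−t)]/(c−t)². For p = 40%, additive: c = 0.35, t = 0.25, so n = 10.507 × 0.415/0.01 = 436.06, rounded up to 437, total 874. The same formula gives all six unadjusted entries exactly: 874, 620 and 452 (additive); 1,156, 820 and 596 (multiplicative).

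**Step 3: reproduce Table 2, adjusted.** Dilute the margins, c′ = c − 0.15(c−t) and t′ = t + 0.05(c−t), recompute n, and divide by 0.95.

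| p | Additive: computed (Table 2) | Multiplicative: computed (Table 2) |
|---|---|---|
| 40% | 1,428 (1,455) | 1,893 (1,812) |
| 50% | 1,019 (1,034) | 1,348 (1,297) |
| 60% | 748 (752) | 986 (941) |

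The additive column agrees within 2%. The multiplicative column of Table 2 is 4-5% lower than computed. Leaving out the division by 0.95 gives 1,798, 1,280 and 936, within about 1% of the table, so that column may omit the allowance for loss.

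**Step 4: power at 1,200.** After 5% loss, 1,200 × 0.95/2 = 570 per margin. Power = Φ( (c′−t′)/SE − 1.960 ), with SE = √{[c′(1−c′) + t′(1−t′)]/570}.

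| p, model | c′ | t′ | c′−t′ | SE | Power |
|---|---|---|---|---|---|
| 40%, additive | 0.3350 | 0.2550 | 0.0800 | 0.0269 | 84% |
| 40%, multiplicative | 0.3369 | 0.2669 | 0.0700 | 0.0271 | 73% |
| 50%, additive | 0.4188 | 0.3188 | 0.1000 | 0.0284 | 94% |
| 50%, multiplicative | 0.4211 | 0.3336 | 0.0875 | 0.0286 | 86% |
| 60%, additive | 0.5025 | 0.3825 | 0.1200 | 0.0292 | 98% |
| 60%, multiplicative | 0.5053 | 0.4003 | 0.1050 | 0.0293 | 95% |

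**Step 5: placebo rate needed for 90% power.** Solving step 4 for p gives about 45% (additive) and 54% (multiplicative). Log-linear interpolation in Table 2's own adjusted columns gives:

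- additive: 40% + 10% × ln(1455/1200)/ln(1455/1034) = 45.6%
- multiplicative: 50% + 10% × ln(1297/1200)/ln(1297/941) = 52.4%

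The thresholds are therefore about 45% and about 52-54%.

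**The case against.** The two sections do not flatly contradict each other. The Discussion is hedged (may, could, uncertain), gives no local rate, and never says that local failure is below 50%. The sample size section does not adopt 60% either: it plans on 50% and tabulates 40%. Doubting a high rate and planning on a discounted one are compatible. Table 2 openly shows that the 40% row needs more than 1,200, and the text claims only general adequacy. The Background states the design hypothesis as additive, and under that model power at 40% is still 84%, above the 80% used for the primary outcome. The Background also reports that 50% of new patients in Australia and New Zealand start haemodialysis with a catheter because of a failed or inadequate fistula.

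Much of this stands, and it limits the point. What it does not supply is a reason for stopping at 50%. The catheter figure is not cited for that purpose and is not a 6-month functional failure rate. The assurance expressly covers the multiplicative model, where 1,200 falls short of Table 2's own 1,297 at 50%.

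A reader might go further and note that primary failure "ranges between 20–54%, due to thrombosis or failure of maturation", so that 50% lies near the top of the protocol's own range, and might then compute power at 30%. The documents do not support this. That range is for primary failure, whereas this outcome is functional patency at 6 months. The two can differ widely: the US placebo group had 19.5% thrombosis but 60% unsuitability for dialysis. No source in the document gives 30% for this endpoint.

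**Conclusion.** The point holds in a limited form. The rate of at least 50% has one stated support, which the Discussion treats as unexpectedly high and of uncertain transfer, and the size of the discount from 60% is unexplained. General adequacy of 1,200 at 90% power under either model is therefore not established. The shortfall is moderate: at 40%, power is about 6 points below target under the additive model (84%) and 17 points below under the multiplicative model (73%). At 50%, only the multiplicative model falls short (86%).

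These figures assume the section's own effect size, drop-in, drop-out and loss, with dilution applied to the marginal rates. They do not show that the local rate is below 50%; the document gives no data to settle that. The primary outcome and its sample size are unaffected.

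**What to change.** Reconcile the secondary sample size section with the first implication in the Discussion. Either give a reason, preferably local data, for treating the US rate as a guide and for the step down to 50%, or withdraw the statement of confidence.

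Replace the assurance of adequacy with the power of 1,200 at the three tabulated rates (additive/multiplicative): about 84%/73% at 40%, 94%/86% at 50% and 98%/95% at 60%. Add that 90% power needs a placebo failure rate of about 45% (additive) or about 52-54% (multiplicative).

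Keep 1,200. The change takes a few lines, with no extra patients and no change to design or analysis. Its one drawback is a less favourable statement of adequacy for this secondary outcome.

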### Recruitment

Based on data from the ANZDATA renal registry[40], 7,202 patients were receiving dialysis in Australia and New Zealand in December 2004. Importantly, 2042 patients commenced dialysis in Australia and New Zealand in the calendar year 2004. Data obtained from the whole of New Zealand population and access rates for Princess Alexandra Hospital (PAH), Queensland, reveal that 1 procedure is performed per year for every 2.3 – 2.8 patients receiving haemodialysis (total numbers of patients – new patients and prevalent patients). The New Zealand data was obtained by [name] (survey from October 1 2000 until September 30, 2001) and by [name] (Queensland) based on prospectively collected data in PAH renal unit from January 2004 until December 2004. In addition further information from the 2005 registry report supports these data. Incident patients require access for dialysis and 27% and 33% of haemodialysis patients in Australia and New Zealand, respectively, were incident patients in 2004. Thus we can expect these patients at the very least to require new vascular access, in addition to existing patients on dialysis who need further access because of failure of previous vascular access procedures. Extrapolation to the whole Australian and New Zealand population, using a conservative estimate of 1 procedure per 3 patients allows us to derive that 2,400 access procedures are performed per year (AVF and AVG). Using a conservative estimate that 75% of access is AVF and not AVG, gives an estimation of 1,800 de-novo AVF creations per year. Assuming we will recruit 22% of these, recruitment should take approximately three years.

This trial is to be conducted by the Australasian Kidney Trials Network (AKTN). The Australian and New Zealand Society of Nephrology, and Kidney Health Australia were instrumental in the development of the AKTN, which is supported by all the major renal units in Australia and New Zealand. The Scientific Committee is representative of the majority of large renal units in Australia and New Zealand. Moreover, the trial has been developed to be as inclusive as possible with an early and relevant primary end-point which should also encourage enrolment. In addition, the Australian and New Zealand renal community has a keen focus on vascular access which has been the subject of a number of recent seminal publications in the area of vascular access. Thus we are confident this trial will be well supported by renal units in Australia and New Zealand.

### Analysis

Analysis of the primary outcome (patency) will be on an intent-to-treat basis. All randomised patients will be analysed in the group they were allocated to, even if they do not receive treatment as allocated, or do not commence treatment. All randomised patients will be included in the analysis.

The primary outcome is measured as the proportion with failure of patency at three months after randomisation. The primary hypothesis will be tested using a chi-square test of proportions to test the null hypotheses that a) the proportion of failures in those allocated to aspirin versus those allocated to placebo aspirin is equal, and b) the proportion of failures in those allocated to omega-3 fatty acids versus those allocated to placebo omega-3 fatty acids is equal. The primary outcome will be measured at 84 days after randomisation, with a permitted tolerance of 7 days prior, and 14 days after the due date of 84 days. Tests of hypotheses will be at the 5% significance level, and 2-sided p-values will be used.

Any patient who does not have a 84-day measure will be counted as failure of patency in the primary analysis. A secondary analysis will be done including only those with a 84-day measure to test the sensitivity of the analysis of the main treatment comparisons to patient exclusions. As this is a short-term intervention, with a relatively short recruitment period, the only planned interim analysis is of safety. This will be conducted at 1/3 and 2/3 of total patient numbers accrued. Similar analyses to the primary one will be undertaken on the secondary outcomes, as well as exploratory analyses looking at the validity of the chosen primary outcome and its correlation with other outcomes, and the prediction of thrombosis from baseline variables such as markers of inflammation.

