### Outcome measures

The **primary outcome measure **is (unassisted) patency of the AVF at three months after randomisation. This is defined as the presence of an audible bruit throughout systole and diastole over the site of the arterio-venous anastomosis, without the need for surgical or radiological intervention from the time of creation until the time of assessment. The assessment of patency will be made at this time even if the AVF is not yet used for haemodialysis[11].

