### Study Procedures

Participants will be recruited from public and private hospital renal units providing haemodialysis and vascular access services in Australia and New Zealand. Patients will meet the inclusion and exclusion criteria and be scheduled to undergo surgery for creation of a de novo AV fistula. Processes to identify and screen all potential recruits will be established within each centre with consultation with the Trial Management Committee.

Patient consent forms will be approved by the Human Research Ethics Committee at each participating site prior to the beginning of the trial. A sample consent form and patient information sheet is provided to participating sites. Participating sites will file a copy of the approved consent form and information sheet for their site with the coordinating office. After discussing the trial, ample time will be given to the participant, accompanying person or legal representative to inquire about the trial and decide whether to participate. No person involved with the trial will coerce or unduly influence the decision of a patient to participate in a trial. A copy of the signed consent form and the patient information sheet will be supplied to the participant. Patient consent must be obtained prior to the registration or initiation of trial procedures. Patients will not be randomised until a signed consent form is filed at site and notification is received by the coordinating office.

The Trial Management Committee will monitor the medical literature, and any other relevant information impacting on the continuation of the trial. Consent forms and patient information sheets will be revised should any relevant and important new information become available.

Registration will occur when subjects come for their surgical consultation prior to the operation to create the AVF. The patient will have an initial consultation with a study renal physician or surgeon to discuss study participation. This will include a preliminary eligibility check. Consenting patients will be registered by emailing or faxing a completed registration form to the coordinating centre. The registration form also serves as notification of completion of a patient consent form. The patient will also be randomised at this time. Stratification will occur for study site, incident versus prevalent patient status and upper vs. lower arm site. Patients will be randomised to one of four treatment groups in equal proportion.

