### Statistical Considerations

#### Sample size calculation for the primary outcome

The event rate for the primary outcome (failure of primary patency) is estimated to be 25% at three months in the control group. If a 30% relative risk reduction is achievable with either aspirin or omega-3 fatty acids, then with 80% power and a significance level of 5%, 1200 study subjects will be required (300 receiving double placebo, 300 active aspirin and placebo omega-3 fatty acids, 300 active omega-3 fatty acids and placebo aspirin, and 300 both active aspirin and active omega-3 fatty acids in a factorial design). This allows for 5% drop-in from placebo to active treatment (either aspirin or omega-3 fatty acids), 5% drop-out from study treatment (to no treatment – assumed equivalent to placebo), and 5% loss to follow-up. This is equivalent to an observed relative risk reduction of 24%. Without adjustment for compliance, the study size needed would have been 932 subjects.

The study is not adequately powered to detect a clinically important difference between the combination of aspirin and omega-3 fatty acids and either treatment alone, but preliminary data on the combination will be obtained. The event rate of the primary outcome, primary failure, is based on review of all papers published in this area. The effect size, a 30% reduction, is based on the smallest size of the effect the proposing clinicians believe would lead to a change in practice (incorporation of intervention) should the trial prove the intervention is efficacious.

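### The primary analysis scores patients without an in-window 84-day measure as failures even where later records show patency, and, separately, the stated 80% power does not belong to that rule

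*Protocol article*

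**What the plan says.** The Outcome measures section defines the primary outcome as unassisted patency at three months: an audible bruit over the anastomosis, "without the need for surgical or radiological intervention from the time of creation until the time of assessment". The Analysis section sets the measurement at 84 days after randomisation, allowing 7 days before and 14 days after, and includes all randomised patients. On missing measures it says: "Any patient who does not have a 84-day measure will be counted as failure of patency in the primary analysis". An observed-only analysis is planned as a sensitivity check.

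Table 1 schedules a record of fistula status at weeks 1, 6 and 12 and again from 6 to 36 months. The Secondary outcome measures section promises at least 12 months of follow-up and collects time to first intervention.

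On size, the protocol says: "The event rate for the primary outcome (failure of primary patency) is estimated to be 25% at three months in the control group". The effect it assumes for each agent is a relative reduction of 30%. The size it derives from these two figures is stated as follows: "then with 80% power and a significance level of 5%, 1200 study subjects will be required". The allowances are 5% drop-in, 5% drop-out "and 5% loss to follow-up". The protocol gives 932 as the size without adjustment for compliance, and 24% as the observed relative reduction after adjustment.

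**The concern.** There are two concerns, and they should be kept apart.

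**Classification.** The outcome accumulates from creation of the fistula. A patient who misses the day 77 to 98 visit, but is later recorded with a patent fistula and no intervention, had no intervention before day 84. Unless a failed fistula can reopen unaided, that patient was also patent at day 84. The rule makes no exception, so the trial would hold evidence of success and count a failure in its primary analysis.

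**Power.** Removing lost patients from the denominator costs sample size. Adding them as failures to both arms raises both failure rates and shrinks the difference between them. These are different calculations. If 1,200 was derived from the first and the analysis does the second, the stated 80% describes a test that will not be run.

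**Working it through.** **Inputs from the protocol.** Control failure 25%; relative reduction 30%, so 17.5% on active treatment; 80% power; 5% level with "2-sided p-values will be used"; total 1,200. Allocation: "Patients will be randomised to one of four treatment groups in equal proportion". Each marginal comparison is therefore 600 vs 600. Drop-in, drop-out and loss are 5% each.

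**Method.** Two-proportion z-test with pooled variance under the null and no continuity correction. With p̄ = (p₁ + p₂)/2, the size per arm is

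n = [1.96·√(2p̄(1−p̄)) + 0.8416·√(p₁(1−p₁) + p₂(1−p₂))]² / (p₁−p₂)²

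Power is the same expression solved for the second normal quantile.

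**Step 1: the unadjusted size.** 25% vs 17.5% gives n = 465.8, rounded up to 466 per arm, or 932 in total. This matches exactly.

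**Step 2: the adjusted size.**
- Control with 5% drop-in: 0.95 × 25 + 0.05 × 17.5 = 24.625%.
- Active with 5% drop-out: 0.95 × 17.5 + 0.05 × 25 = 17.875%.
- Relative reduction: 1 − 17.875/24.625 = 27.4%.
- Total needed: 1,150.7, or 1,152 in whole patients per arm. Dividing by 0.95 gives 1,211 to 1,213, about 1% from the stated 1,200.
- With 570 evaluable per margin (0.95 × 600), power is 79.6%.

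So 1,200 with 80% power is what results when the lost 5% leave the denominator.

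**Step 3: the rule in the Analysis section.** With a fraction m missing, equal across arms and unrelated to true patency, the scored failure rate is p′ = m + (1 − m)p, and all 600 per margin stay in.

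| Missing | Control | Active | Relative reduction | Power at 1,200 | Total for 80% |
|---|---|---|---|---|---|
| 0% | 24.6% | 17.9% | 27.4% | 81.6% | 1,152 |
| 2% | 26.1% | 19.5% | 25.3% | 78.0% | 1,262 |
| 5% | 28.4% | 22.0% | 22.6% | 72.6% | 1,438 |
| 10% | 32.2% | 26.1% | 18.9% | 63.9% | 1,754 |

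The 5% row is the protocol's planned loss. The 2% and 10% rows are assumptions that show the range.

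**Step 4: a different assumption about the missing.** Keep the overall rates at 24.625% and 17.875%, and let the 5% missing carry no treatment effect. If a share q of them are true failures, each arm's scored rate rises by 0.05 × (1 − q). Power is 75.8% at q = 0, 78.5% at q = 0.5 and 81.6% at q = 1.

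**Step 5: what reclassification can recover.** Under the Step 3 assumptions with 5% missing, power is 72.6% if no missing status is recovered, 77.1% if half is, 79.4% if three quarters is and 81.6% if all is.

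**The case against.** **The two defects are not one.** A reader might infer that misclassifying fistulas known to be patent is what takes power down to 73%. The documents do not support that. The 72.6% comes from scoring the whole planned 5% loss as failures, and patients who are truly lost have no later visit. The group that misses the window but is seen again has no stated size. If it is 1 of the 5 percentage points, reclassification lifts power only from 72.6% to 74.4%. This objection stands.

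**Removal from the denominator is inferred.** The protocol says only that the total allows for 5% loss. Its stated observed reduction of 24% fits neither account: drop-in and drop-out alone give 27.4%, and adding missing = failure gives 22.6%. Scoring the 5% as failures with no drop-in or drop-out would give 24.8% and 81.2% power, but that ignores two allowances the protocol says it made. With all three applied, removal comes close to 1,200 and missing = failure does not (1,438). The inference is sound, but it remains an inference.

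**Late visits.** The Analysis section does not spell out how an assessment after day 98 is handled, and an analysis plan that is not shown may do so. As written, the rule offers such a patient no route to success.

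**Comparability.** The primary assessment uses two independent blinded observers. Nothing says the later visits do, or that they apply the same bruit criterion. This is a real but small cost of using later records.

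**Differential missingness.** A reader might also infer that the rule biases the comparison, because the Background names gastrointestinal complaints with omega-3. If both arms truly failed at 25% and missingness were 4% vs 6%, scored failure would be 28.0% vs 29.5% with no drug effect. But those missing rates are only illustrative. The protocol analyses patients as allocated whether or not they take treatment, so stopping capsules is not the same as missing the visit. Bias is a possibility, not a finding.

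**Validity.** The rule is prespecified, keeps every randomised patient and has an observed-only check. When missingness is balanced the test remains valid. That check, however, also discards the later observations and does not restore the power of the primary test.

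**Conclusion.** Both points hold, separately.

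1. The rule scores as failures some patients whose later records would show patency without intervention. This rests on the cumulative definition and on the ordinary assumption that a failed fistula does not reopen unaided. The protocol gives no basis for the number affected, so no size can be attached to it.

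2. The stated 80% does not describe the planned primary analysis. Under that rule, power at 1,200 is about 73% if missing measures equal the planned 5% loss, are equal across arms and are unrelated to patency. It is 78% at 2% and 64% at 10%. If the overall arm difference is kept and the missing carry no treatment effect, it is about 76% to 82%. All of these figures take the protocol's own 25% vs 17.5% as the marginal contrast.

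The shortfall is therefore conditional, and 73% is one scenario within a range.

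**What to change.** **Change the classification rule**, before unblinding, since it defines the primary outcome:
- If the 84-day measure is missing or out of window, classify from recorded bruit and intervention status. Patent and intervention-free at a later visit counts as patent at day 84. A recorded failure or intervention by day 84 counts as failure.
- Score missing as failure only when no such information exists.
- Keep the observed-only analysis as a sensitivity check, and state whether later visits use the same bruit criterion and observers.

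**Restate the primary power** under the rule that will be used, giving the assumed missing rate and a range. Say how the 5% loss enters the calculation, and reconcile it with the stated 24% observed reduction.

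The cost is a few lines of text and a derivation from data already scheduled for collection. The price is a less favourable power statement and some mixing of assessment conditions within the endpoint. Patients never seen again cannot be reclassified. With 5% missing, power after the change therefore lies between 72.6% (none recovered) and 81.6% (all recovered).
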